| 4-6 hr Fasting Glucose                     |                                  | X                                           |                                  |                                  |                      |                |
| Resource Assessment                                    |                                  |                                             |                                  |                                  |                      | X              |
| Sub-Study IPCARD Questionnaire                         |                                  | X                                           |                                  |                                  | X                    |                |
|  F  FDG-PET  |                                  | X                                           |                                  |                                  |                      |                |
| DCE-CT                                   |                                  | X                                           |                                  |                                  |                      |                |
| Chest CT                                 |                                  |                                             | X                                | X                                |                      | X  |
| Concomitant Medications                                | X                                |                                             |                                  |                                  |                      |                |
| Adverse Events                             |                                  | X                                           |                                  |                                  |                      |                |

 Method in accordance with standard hospital procedure for FFDG-PET.

 Chest CT scans will be performed only on patients without definitive pathological findings

 FFDG-PET and DCE-CT scans will be performed on the same day. If not possible, they should ideally be done within 14 days but no longer than 21 days.

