### 5.2 PATIENT MANAGEMENT FOLLOWING PET-CT AND DCE-CT

Following the PET-CT and DCE-CT investigations, management of the SPN should be directed by the local/specialist lung MDT.

In many cases nodule biopsy or excision biopsy may be undertaken. Those cases shown to be due to lung cancer (or other malignancy) will be managed according to local protocols. Follow up/outcome data will be collected by CRF.

In some cases it is recognised that nodule surveillance is appropriate (with or without prior biopsy). In these cases it is recommended that follow up is performed at

- 3 months
- 9 months
- 24 months

as per Fleischner Society Guidelines (Radiology 2005;237:395) for management of indeterminate nodules >8mm. (Deviation from these time points based on clinical need is at the discretion of the MDT)

At each visit the following should be performed:

- Chest CT (low dose, thin section, unenhanced) unless MDT feels it is inappropriate
- Recording of any biopsy samples taken

- Recording of health resource use information

At 2 years

- Health resource data will be collected from patient records
- The end of study CRF will be completed in the InForm Database
- The PI will sign off the patients electronic CRF record and the database will be locked for that patient

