## **7 DEFINITION OF END OF TRIAL**

This is a non-CTIMP study with all eligible patients recruited consecutively into the study and undergoing each study procedure. Recruitment will be terminated once 375 patients have been recruited and undergone a DCE-CT scan.

The study has two possible endpoints for each patient:

**Either** the diagnosis of lung cancer via biopsy **or** a diagnosis of benign or non- lung cancer via either biopsy (please note that in this case economic data collection will continue to be required for 2 years follow up)

**Or** failure of the imaged nodule to progress (increase in size) during the 2 year follow up period.

The end of the study will be reached when the last study patient reaches two years of follow up or withdraws full consent for continuing in the study.

**PLEASE NOTE:** *Health Resource Data will be collected for all patients over a 2 year period following the DCE-CT scan, therefore the end of study form will not be completed until this time unless patients have withdrawn full consent.*

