## **10 ASSOCIATED STUDIES**

### **10.1 IPCARD-SPN STUDY (APPENDICES 6-7)**

The IPCARD study is a semi- validated symptom questionnaire which investigates the diagnostic potential of a range of general and respiratory patient reported symptoms in the diagnosis of lung related diseases.

- Patients will be asked to complete the IPCARD questionnaire at the start of the study following consent
- Patients who have not had a cancer diagnosis after one year of follow up will be sent a second copy of the questionnaire to Research teams at site will check patient notes within 1 week of posting a second IPCARD questionnaire to ensure that patients have not received a cancer diagnosis, are not terminally ill or have not died since consenting to the trial

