#### **RECRUITMENT STRATEGY AND CONSENT**

Potential SPUtNik participants will be introduced to the IPCARD-SPN study by the research nurse or PET coordinator either by phone or in clinic. They will be given the IPCARD-SPN questionnaire along with the SPUtNik patient information sheet, which contains a section about the IPCARD-SPN study.

The questionnaire contains no identifiable patient information. Patients may fill in the questionnaire prior to attending the scan appointments and bring it along to the scan appointment. At the scan appointment the research nurse or radiographer will take consent for the SPUtNik study, which includes an optional part for the IPCARD-SPN trial. If the patient consents to the IPCARD-SPN trial, the SPUtNik trial code will be added to the front of the questionnaire and completed questionnaires can be left with the research nurse. For incomplete questionnaires the SPUtNik code will be added and the patient given a Free-Post return envelope and asked to return the questionnaire by post within 2 days.

Participants will be told that they may withdraw consent at any time by telephoning the local hospital site a number is given on the patient information sheet.

Date received will be recorded for returned questionnaires and they will be prepared for automated data entry. Diagnosis will be obtained two years following recruitment from SPUtNik Trial data.

A second copy of the IPCARD questionnaire will be posted to all patients who have not received a lung cancer diagnosis after 1 year (12-18 months) of follow up. This copy will contain the SPUtNik code and be clearly marked IPCARD2. It will be posted with a cover letter explaining why the patient has been asked to complete the questionnaire for a second time and a prepaid envelope to return the questionnaire to SCTU.

Research staff, are instructed to ensure questionnaires are not sent to patients that have already received a diagnosis of lung cancer, are terminally ill or have died.

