## DATA ANALYSIS

The predictive value of symptoms for lung cancer diagnosis will be identified at 12 (12 months from recruitment/questionnaire completion) and 24 months following questionnaire completion (end of study) for the first IPCARD questionnaire, and at 12 months following questionnaire completion (2 years from recruitment/ at end of study) for the second IPCARD questionnaire.

Logistic regression will be used to obtain unadjusted and adjusted odds ratios for symptoms. The models will be adjusted for age, sex and current smoking status and COPD status. COPD precedes lung cancer diagnosis in 40% to 90% of the cases and differences in prevalence of COPD between early stage and late stage lung cancer might explain differences in symptoms between these groups [14].

COPD will be defined by:

- Abnormal spirometry post-bronchodilator: defined as a forced expiratory volume in 1 second (FEV1) <70% of predicted and forced expiratory volume in 1 second/ forced vital capacity (FEV1: FVC) ratio <0.70. This is based on the American Thoracic Society standards agreed by most respiratory guidelines.

AND/OR

- Clinical diagnosis, by the chest clinic physician, based on the presence of symptoms such as recurrent cough (productive), wheezing, dyspnoea in conjunction with pre-disposing risk factors such as smoking, age and family history.

This data will be drawn from patients' medical records by research staff and will not be taken as part of the study

For the purposes of this study the implications of using a second definition of COPD (based upon evidence of emphysema identified by CT scan) will also be explored. It is possible that early symptoms experienced by those with resectable lung cancer might be explained by emphysema.

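### The second IPCARD questionnaire is given a 12-month prediction horizon, but its 12-18 month posting window and the month-24 outcome date allow only 6 to 12 months

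*Protocol*

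**What the plan says.** All references are to the Protocol.

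- **Stated horizon.** Appendix 6, Data analysis, evaluates symptoms on the second questionnaire "at 12 months following questionnaire completion (2 years from recruitment/ at end of study"). Completion plus 12 months is thus treated as the same date as month 24.
- **Posting window.** Appendix 6, Recruitment strategy and consent, has the form "posted to all patients who have not received a lung cancer diagnosis after 1 year (12-18 months) of follow up". The Schedule of Observations has a row for the "Sub-Study IPCARD Questionnaire" with marks at baseline and at Visit 4, and Visit 4 is headed 12-18 months. Section 10.1 gives no upper limit: "Patients who have not had a cancer diagnosis after one year of follow up will be sent a second copy of the questionnaire".
- **Outcome date.** Appendix 6 states: "Diagnosis will be obtained two years following recruitment from SPUtNik Trial data".
- **Data closure.** Among the tasks at 2 years, Section 5.2 lists: "The PI will sign off the patients electronic CRF record and the database will be locked for that patient". Section 7 closes the trial as a whole later: "The end of the study will be reached when the last study patient reaches two years of follow up".
- **Method.** Appendix 6 plans univariate and stepwise logistic regression, then a symptom score with sensitivity, specificity and predictive values at several cut-offs. None of this text refers to differing time at risk.
- **Dates held.** For returned questionnaires, the only date that Appendix 6 says will be recorded is the date of receipt.

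**The concern.** A predictive value has a meaning only with its time horizon. The Protocol attaches one horizon, 12 months, to forms whose distance from the outcome date varies by a factor of two. A patient observed for 6 months after the form and one observed for 12 are both coded as non-cancer if undiagnosed at month 24, and a logistic model without a time term treats them alike.

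The form goes only to people still undiagnosed when it is sent. Someone diagnosed in month 15 can contribute an event if the form was completed at month 12, but never receives one if posting was planned for month 18. The late-form group has therefore been screened for survival without diagnosis over a longer period. Its event probability to month 24 is probably lower, which would lower the positive and raise the negative predictive value. If posting time also differs between sites, it becomes a nuisance factor in the symptom comparisons.

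Predictive values of symptoms are the first stated aim of the sub-study, so the label belongs to a headline quantity of the second-questionnaire analysis.

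**Working it through.** **Inputs.** Completion month t = 12 to 18 (Appendix 6; Schedule, Visit 4). Outcome date: month 24 (Appendix 6; Section 5.2). Stated horizon: 12 months (Appendix 6).

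**Step 1: reproduce the stated equality.** With t = 12, 24 − 12 = 12 months. The Protocol's two descriptions agree at this point.

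**Step 2: the rest of the window.** Available horizon = 24 − t. Month at which a full 12-month horizon would end = t + 12.

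| Completion month t | Horizon to month 24 | End of a full 12-month horizon |
|---|---|---|
| 12 | 12 | 24 |
| 13 | 11 | 25 |
| 14 | 10 | 26 |
| 15 | 9 | 27 |
| 16 | 8 | 28 |
| 17 | 7 | 29 |
| 18 | 6 | 30 |

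A common 12-month horizon would need diagnosis data to between months 24 and 30. The Protocol provides for none after month 24. The form is posted only after one year and comes back by post, so nearly every form will fall short of 12 months, some only slightly.

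If completion were uniform over the window (an assumption), the mean horizon would be 24 − 15 = 9 months. That is 9/12 = 75% of the stated figure.

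**Step 3: what this could do to event probability.** The Protocol gives no rate of diagnosis after month 12, so only illustrations are possible.

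*Illustration A, constant hazard after the form.* Risk over h months = 1 − (1 − R)^(h/12), where R is the 12-month risk. This is conditional on being undiagnosed at the form, which matches the posting rule.

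| R (assumed) | h = 9 | h = 6 |
|---|---|---|
| 5% | 3.8% | 2.5% |
| 10% | 7.6% | 5.1% |
| 20% | 15.4% | 10.6% |

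*Illustration B, every later diagnosis comes from the 24-month CT.* Sections 5.2 and 8.4 place CT at 3, 9 and 24 months, with none between 9 and 24. In this case no one is removed between months 12 and 18, and the probability of diagnosis by month 24 does not depend on t. The effect is zero.

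The illustrations run from roughly a halving for a month-18 form to no change. The Protocol does not say which is nearer the truth.

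**The case against.** The strongest defence is that the outcome date is not in doubt. The parenthesis in Appendix 6 names two years from recruitment, and the recruitment section repeats it. On that reading the analysis is already lung cancer between form and month 24, and only the 12-month label is wrong. Most of this stands. It makes the correction easy, but it does not deal with unequal time at risk under a single label.

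A second defence is that the end of the study means the end of the whole trial, which gives earlier recruits more time. It fails. The parenthesis gives two years from recruitment as the same time point, Section 5.2 locks each patient's record at 2 years, and the last patient recruited would gain nothing.

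Three stronger readings are tempting, and the Protocol does not support them:

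- A reader might infer that a 12-month horizon is impossible. It is met at month 12, and Section 10.1 describes the mailing simply as after one year.
- A reader might infer that late responders have cancers of months 6 to 12 after the form miscounted as benign. For a month-18 form those are cancers of months 24 to 30. They are unobserved for every patient, because the reference standard in Section 8.4 closes at 24 months for all. The late group differs through the removal of cancers diagnosed before its forms are posted.
- A reader might take 25% less mean time as 25% fewer diagnoses or a PPV 25% lower. Time lost is not events lost: with no CT scheduled between months 9 and 24, the effect could be much smaller.

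**Conclusion.** The point holds as an internal inconsistency in a stated analysis horizon. It is not a detail left for a later analysis plan. The true horizon is 6 to 12 months, and the stated one is right only for a form completed at exactly month 12. That conclusion rests on the posting window, the two-year diagnosis date and the per-patient lock alone.

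The direction of the effect on predictive values, lower PPV and higher NPV for later forms, is plausible. Its size cannot be derived from the Protocol. The mean of 9 months needs uniform completion, and the risk figures need an assumed 12-month risk and a constant hazard.

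The point is minor. It touches only the second-questionnaire analysis of the optional IPCARD-SPN sub-study. The main accuracy analyses, the economic model and the first-questionnaire analyses at 12 and 24 months are unaffected.

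**What to change.** In Appendix 6, Data analysis:

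1. Define the second-questionnaire outcome as lung cancer diagnosed between the form and month 24. Describe the horizon as 6 to 12 months and drop the 12-month label.
2. State the time origin. The receipt date is already recorded and will serve; recording the completion date would be better.
3. Account for time from form to month 24, for example as a covariate or offset in the regression, or with a simple Kaplan-Meier or Cox analysis from the form date. Section 9.1(ii) already relies on exact dates of diagnosis or censoring. Its spline model is written for the imaging tests and is more than is needed here.
4. Report the observed distribution of the horizon beside the predictive values.

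Alternatively, narrow the posting window to about month 12 in Appendix 6 and the Schedule, so that the stated horizon is nearly true.

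The first route needs no further follow-up. It costs a wording change, a little extra analysis and a less tidy horizon. The second leaves sites less room in scheduling the mailing.

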#### **SAMPLE SIZE**

Sample size calculations for the analyses (assuming a two sided 5% alpha) using 257 cases of lung cancer and 118 without LC, gave 80% power to detect a difference in a rare or low frequency variable of 10% (from 5% in non-LC to 15% in LC) or 80% power to detect a difference in a more common variable of 14% (from 16% in non-LC to 30% in LC or from 22% in non-LC to 36% in LC). For a more prevalent LC symptom, 257 cases of lung cancer and 118 without LC gave 80% power to detect a difference of 16% (from 34% in non-LC to 50% in LC). The SPUtNik Trial, which anticipates identifying 257 cases of LC and 118 non-malignant lesions, is adequately powered to detect odds ratios for all symptoms (except rare symptoms) likely to have diagnostic value (>2 or <0.5) in clinical populations.

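### The second IPCARD questionnaire excludes every cancer diagnosed before 12-18 months, yet it shares the 257-cancer power basis and the full adjusted, stepwise analysis plan

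*Protocol*

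**What the plan says.** All of this is in Protocol Appendix 6 (IPCARD-SPN), apart from the CT schedule.

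- **Who gets the second form.** Under Recruitment Strategy and Consent, the second questionnaire "will be posted to all patients who have not received a lung cancer diagnosis after 1 year (12-18 months) of follow up". It is also withheld from patients who are terminally ill or have died.
- **When its outcome is read.** Data Analysis plans predictive values at 12 and 24 months for the first form, and "at 12 months following questionnaire completion (2 years from recruitment/ at end of study) for the second IPCARD questionnaire".
- **Which model.** The next paragraph reads "Logistic regression will be used to obtain unadjusted and adjusted odds ratios for symptoms", with adjustment for age, sex, current smoking and COPD. The text that follows adds comorbidities, interactions, a univariate screen at p<0.05, forward stepwise selection and a simple symptom score. None of it distinguishes the two questionnaires.
- **Power.** The Sample Size paragraph begins "Sample size calculations for the analyses (assuming a two sided 5% alpha) using 257 cases of lung cancer and 118 without LC" and claims 80% power for symptom rates of 5% v 15%, 16% v 30%, 22% v 36% and 34% v 50%.
- **Late cancers.** Section 8.4 schedules CT at 3, 9 and 24 months for patients without definitive pathology. No count of cancers expected after 12-18 months is given.

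**The concern.** The protocol creates a second data set whose members are chosen for not yet having the outcome, and then offers for it a power basis and a modelling strategy written for the whole cohort. The 257 cancers include all those diagnosed soon after the scans, and none of these can contribute to the second questionnaire. The smallest adjusted model has five parameters (one symptom and four covariates) before any comorbidity, interaction or further symptom is added.

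Two things are at stake. Symptoms that do predict a later diagnosis will mostly be missed. And because only symptoms with univariate p<0.05 go forward, those that do go forward will tend to carry an odds ratio well above the truth, and these are the ones that would feed a model and a score.

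**Working it through.** **1. The plan's own figure.** Inputs: 257 cancers, 118 non-cancers, two-sided 5%. With the pooled two-proportion formula, power = Φ{[|p2−p1| − 1.96·√(p̄(1−p̄)(1/n1+1/n0))] / √(p1(1−p1)/n0 + p2(1−p2)/n1)}.

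For 34% v 50%: p̄ = (118×0.34 + 257×0.50)/375 = 0.450. The numerator is 0.160 − 1.96×0.0553 = 0.0516 and the denominator is 0.0536, so z = 0.96 and power is 83.2%. All four contrasts:

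| Symptom rates | Uncorrected | Continuity-corrected |
|---|---|---|
| 5% v 15% | 83.8% | 78.2% |
| 16% v 30% | 84.5% | 80.9% |
| 22% v 36% | 78.8% | 74.9% |
| 34% v 50% | 83.2% | 80.1% |

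The stated 80% is reproduced to within a few points. It is sound for the first questionnaire.

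**2. Events for the second questionnaire.** A form sent at 12-18 months leaves 24−12 = 12 down to 24−18 = 6 months of follow-up. The number of cancers in that window is not given, so I assume a range. Appendix 6 reports a response rate above 70% in earlier IPCARD work, and I take 70%:

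- 2% of 257 diagnosed late: 257×0.02×0.7 = 3.6, about 4 events
- 5%: 257×0.05×0.7 = 9.0
- 10%: 257×0.10×0.7 = 18.0
- 10% with complete return: 257×0.10 = 25.7, about 26
- Non-cancers: 118×0.7 = 82.6, about 83

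**3. Events per parameter** in the five-parameter model: 4/5 = 0.8, 9/5 = 1.8, 18/5 = 3.6, 26/5 = 5.2.

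**4. Power.** Even with all 118 non-cancers returning forms, the formula in step 1 gives 12-26% across the four contrasts at 5 late cancers, 18-33% at 10 and 34-46% at 26.

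**5. The p<0.05 screen.** With a and b the cancers with and without the symptom, and c and d the non-cancers with and without it, Wald z = ln(ad/bc)/√(1/a+1/b+1/c+1/d). A table with a zero cell counts as not passing. For 34% v 50% (true odds ratio 0.50/0.50 ÷ 0.34/0.66 = 1.94) and 83 non-cancers:

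| Late-cancer forms | Passes screen | Smallest passing OR above 1 | Median OR if passing |
|---|---|---|---|
| 4 | 0.3% | – | too rare to matter |
| 9 | 14% | 4.2 | 6.2 |
| 18 | 24% | 2.9 | 3.7 |
| 26 | 30% | 2.5 | 3.2 |

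Exact enumeration of the 2×2 tables confirms these figures. At 9 events the least extreme table that passes is 5 of 9 cancers against 19 of 83 non-cancers: OR = (5×64)/(4×19) = 4.21, standard error √(1/5+1/4+1/19+1/64) = 0.720, z = 1.44/0.720 = 2.0. An estimate near the true 1.94 cannot pass. The medians are 6.2/1.94 = 3.2, 3.7/1.94 = 1.9 and 3.2/1.94 = 1.6 times the truth. With 118 non-cancers they are about 6.1, 3.6 and 3.0, so the pattern does not depend on the assumed response among non-cancers.

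**6. Non-finite adjusted fits.** These come from simulation with 118 non-cancers and assumed covariate distributions. The share of models with at least one non-finite coefficient, for 5/15%, 16/30% and 34/50%, is 56/34/27% at 5 late cancers, 21/4/2% at 10 and 1/0/0% at 26. Without any screening, the median finite odds ratio for the 34% v 50% symptom is 1.9-2.0 from 5 events upward. For the rare symptom (true 3.35) it is 8.7 at 5, 4.8 at 10 and 3.6 at 26.

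**The case against.** The strongest reply is that the event count is assumed. The protocol gives none, Section 8.4 schedules a 24-month CT for every undiagnosed patient, and it cites doubling times of up to 465 days, so cancers may well surface late. That stands, and it is why every result here is conditional on a stated number of late cancers.

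A reader might also infer that most second-questionnaire models would have no finite solution, that their odds ratios would generally be grossly inflated, or that any symptom reported from them would be an artefact. The documents do not support this. Frequent non-finite fits need about 5 or fewer events, or a rare symptom at about 10. For the 34% v 50% symptom the unselected median is close to the truth. A mean odds ratio would look inflated, but only because its distribution is skewed. No false-positive rate has been shown that would make every reported symptom spurious. The inflation that remains for this symptom comes from selecting on p<0.05.

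Next, the stepwise and score paragraphs never name the second questionnaire, and the sub-study's stated aim is PPV and NPV. This is partly right. But the logistic sentence directly follows the one listing both questionnaires, and nothing exempts the second.

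Finally, the treatment of sparse data usually belongs in a statistical analysis plan. That is true of penalised or exact methods, but here the protocol itself states the power basis and the modelling rule.

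**Conclusion.** The point holds in a limited form. The 257/118 power statement cannot describe the second questionnaire, because all cancers diagnosed before it are excluded by design. The modelling plan as written is too large for the events likely to remain. Over an assumed 4 to 26 returned late-cancer forms, a symptom that the protocol treats as detectable with 80% power passes the screen in about 0% to 30% of data sets. When it passes at 9 to 26 events, its median odds ratio is about 1.6 to 3.2 times the true value. These sizes rest on the assumed late-cancer counts, a 70% return among non-cancers and the protocol's own symptom rates. At 20 or more late cancers the remaining problems are low power, imprecision and selection; failure of the model to fit is then uncommon. This is a minor point: it concerns the second wave of an optional sub-study and leaves SPUtNik's primary diagnostic-accuracy results untouched.

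**What to change.** Change the wording of Appendix 6 only.

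- **Sample Size:** state that the calculation with 257 cancers and 118 non-cancers applies to the first questionnaire only.
- **Data Analysis:** confine the multivariable, interaction, stepwise and score analyses to the first questionnaire.
- **Second questionnaire:** report the number of cancers diagnosed after it, and PPV and NPV per symptom with exact 95% intervals. Any odds ratio should be unadjusted, estimated by an exact or penalised method, and labelled exploratory.

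The cost is that the second questionnaire yields no fully adjusted model. No change to data collection is needed, and what is kept matches the sub-study's stated aim of PPV and NPV.

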Predictive values of symptoms for lung cancer diagnosis obtained from previous research [4, 5] and clinical decision support aids based upon these datasets (e.g. RATS [10]), do not distinguish between early and late stage lung cancer. Existing datasets based upon GP paper records do not provide the power to identify symptoms of early stage disease, and risk scores based upon these datasets assume no difference between symptoms of early and late stage LC. Electronic General Practice Research Database (GPRD) datasets, although providing greater power, do not provide detailed information about symptom experiences or record multiple symptoms with accuracy, information which is likely to be necessary to identify symptoms which predict early stage LC. The SPUtNik study provides a unique opportunity to ascertain whether or not it is possible to distinguish between malignant and non-malignant solitary nodules on the basis of symptoms. The collection of symptom data within SPUtNik will allow the identification of symptoms associated with early malignant disease. Apparent associations of symptoms with LC diagnosis in previous research might be explained by confounding; symptoms might be predictive of chronic respiratory disease or lung lesions more generally. The inclusion of symptom data within the SPUtNik Trial would also enable the identification of symptoms which, when incorporated into a diagnostic algorithm might improve the diagnostic performance of FDG-PET and DCE-CT scans. The IPCARD-SPN study will use the IPCARD symptoms risks, and co-morbidities questionnaire within a prospective study design to identify symptoms which distinguish between malignant and non-malignant solitary nodules.

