Age, sex and further common comorbidities which are found to differ between the LC and non-LC populations, and share symptoms with lung cancer will be included as covariates in the multivariate models. Previous research has found interactions between symptoms and risk factors to have higher PPVs than symptoms alone [6]. Items to identify individual risk of LC were included in IPCARD to determine the interaction of symptoms and established epidemiological risk factors [13], further refining estimates of individual risk in those with symptoms. Clinically plausible interactions between symptoms and interactions between symptoms and risk factors/comorbidities (pack years smoked, family history of cancer, previous malignancy, previous pneumonia, asthma, and acute respiratory infections) will be tested in the final model.

Multivariable analyses –developing a model to predict lung cancer diagnosis: A multivariable model will be developed which will be adjusted for age, sex, current smoking status, COPD status and common comorbidities where these differ between lung cancer and non-lung cancer. Clinically plausible interactions between symptoms, and interactions between symptoms and risk factors/comorbidities (pack years smoked, family history of cancer, previous malignancy, previous pneumonia, asthma, and acute respiratory infections)

will be tested. All symptoms with an association with LC in univariate analyses will be entered into the final model.

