## Section 15 - Smoking History

Q74 Have you ever smoked?  
(Smoking is defined as smoking one cigarette/pipe/cigar a day for as long as one year.)

Yes

☐

Please go to question 75

No

☐

End of questionnaire

Q75 When did you start smoking? Year -----

Q76 What is the total number of years in your life that you have smoked? \_\_\_\_\_

Q77 Do you currently smoke?

Yes

☐

Q77

On average (over your lifetime), \_\_\_\_\_ cigarettes  
how much do you smoke on a \_\_\_\_\_ cigars  
week day? \_\_\_\_\_ oz tobacco

No

☐

Q78  
↗

When did you give up smoking altogether? Year -----

Q79  
↘

On average, how much did you \_\_\_\_\_ cigarettes  
used to smoke on a week day? \_\_\_\_\_ cigars  
\_\_\_\_\_ oz tobacco

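### In the IPCARD-SPN symptom models the only smoking main effect is current status, with its levels undefined; pack-years should be forced in as a main effect and not appear only in interactions to be tested

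*Protocol*

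**What the plan says.** Appendix 6, Data Analysis, fixes the adjustment set twice. For the odds ratios of individual symptoms: "The models will be adjusted for age, sex and current smoking status and COPD status". For the multivariable prediction model, the set is "adjusted for age, sex, current smoking status, COPD status and common comorbidities where these differ" between the lung cancer and non-lung-cancer groups. Neither statement gives the levels of the smoking variable or names a term for cumulative exposure.

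Pack-years does appear in the same section, as a partner in terms to be tested: "interactions between symptoms and risk factors/comorbidities (pack years smoked, family history of cancer, previous malignancy, previous pneumonia, asthma, and acute respiratory infections".

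The modelling-strategy paragraph then enters symptom variables by forward stepwise regression (entry at p ≤ 0.05, removal at p ≥ 0.1). Symptoms found to be independently related to lung cancer each score 1 in a simple sum.

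The questionnaire (Section 15, Smoking History) asks whether the patient ever smoked, the start year, "What is the total number of years in your life that you have smoked", whether they smoke now, the average amount on a weekday (for ex-smokers, the item beginning "On average, how much did you") and "When did you give up smoking altogether".

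**The concern.** Cumulative smoking plausibly raises both the risk that a nodule is lung cancer and the chance of reporting cough, phlegm or breathlessness. A model that holds only current status fixed compares ex-smokers with each other regardless of how much they smoked. A symptom that merely marks heavier past smoking can then keep an odds ratio above 1 after adjustment, pass the stepwise entry rule and be reported as an independent predictor.

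The Appendix 6 background presents the sub-study partly as an answer to doubtful earlier findings: "Apparent associations of symptoms with LC diagnosis in previous research might be explained by confounding". What is at stake is how the adjusted odds ratios are read and which symptoms are selected. The variable needed to reduce the problem is already being collected.

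**Working it through.** The plan gives no figure to reproduce on this point. The check compares the passages and then illustrates the possible size.

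**1. Does the interaction clause supply the main effect?** A conventional hierarchical model that tests symptom × pack-years would also contain pack-years itself. The text, however, places these tests in the final model, and the stepwise rule speaks only of symptom variables. It does not say that pack-years is present while symptoms are being selected, nor that it stays if no interaction is kept. The adjusted odds ratios in the first adjustment statement come with their own covariate list, and pack-years is not on it.

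**2. Does COPD stand in for exposure?** In part. COPD may be defined by spirometry and/or by a clinical diagnosis that itself rests on cough, wheeze, breathlessness and risk factors including smoking. It therefore overlaps with the symptoms under study and does not grade exposure.

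**3. Size, on assumed inputs.** Apart from the 68.5% prevalence, none of these comes from the protocol.
- Smoking: never 15%, ex 55%, current 30%.
- Pack-years (PY): 0 in never-smokers; gamma with mean 2 × 15 = 30 in ex-smokers and 3 × 13 = 39 in current smokers.
- COPD: logit = −2 + 0.03 × PY.
- Lung cancer: logit = a + b1 × PY/10 + 0.3 × COPD, with a set to give 68.5% (the protocol's prevalence).
- Symptom: logit = c + b2 × PY/10 + 0.7 × COPD, with c set to give 35%. The symptom has no effect on cancer given PY and COPD, so its true odds ratio is 1.
- 400,000 simulated patients per row. Age is not included.

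Estimated odds ratio for this null symptom:

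| b1 (cancer) | b2 (symptom) | Unadjusted | Current yes/no + COPD | Never/ex/current + COPD | Same + pack-years |
|---|---|---|---|---|---|
| 0.1 | 0.1 | 1.13 | 1.04 | 1.03 | 1.00 |
| 0.2 | 0.1 | 1.20 | 1.09 | 1.07 | 1.00 |
| 0.2 | 0.2 | 1.32 | 1.18 | 1.15 | 1.01 |
| 0.3 | 0.3 | 1.61 | 1.39 | 1.30 | 1.00 |

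Slopes of 0.1 to 0.3 are odds ratios of exp(0.1) = 1.11 to exp(0.3) = 1.35 per 10 pack-years. The standard error of each log odds ratio is about 1/√(400,000 × 0.35 × 0.65 × 0.685 × 0.315) = 0.007, so 1.01 in the last column is compatible with no bias.

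**4. What that means for selection at p ≤ 0.05.** With at most 375 patients, the standard error of the log odds ratio is about 1/√(375 × 0.35 × 0.65 × 0.685 × 0.315) = 1/√18.4 = 0.233. The chance of a two-sided p ≤ 0.05 is approximately Φ(z − 1.96) + Φ(−z − 1.96), with z = ln(OR)/0.233.
- OR 1.03: z = 0.13, chance about 5%.
- OR 1.15: z = 0.60, chance about 9%.
- OR 1.30: z = 1.13, chance about 20%.
- OR 1.39: z = 1.41, chance about 29%.

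These are slightly high, because adjustment for covariates widens the standard error.

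**5. A second set of assumptions, without COPD.** With 20/50/30% never/former/current, symptom prevalence 25% and yes/no coding, the null odds ratio was 1.05 to 1.55, with rejection in 5.1% to 32.9% of simulated trials of 375. With three-level status plus pack-years it was 1.00 to 1.01, with rejection in 4.3% to 5.9%. This set deserves less weight, because it omits COPD and uses only the least favourable coding.

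**The case against.** The strongest defence is that the sub-study is largely predictive. It seeks predictive values and added diagnostic value, and it judges the score by sensitivity and specificity. A symptom that marks smoking exposure can be a legitimate predictor there. That stands. The point therefore concerns only adjusted odds ratios and the claim of an independent relationship, both of which the plan also makes.

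The plan also has partial controls: every participant has a nodule, age and COPD are adjusted for, comorbidities that differ between groups are added, and an emphysema-based definition of COPD will be explored. That stands too, and lowers the likely bias.

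Four stronger readings might be inferred, and the protocol does not support them:
- *Ex-smokers are pooled with never-smokers.* This follows only if the variable is yes/no. The levels are undefined, and the questionnaire allows never/former/current.
- *Pack-years is ignored.* It is named, but only inside interactions.
- *The plan leaves its own stated confounding concern unaddressed.* The background sentence goes on to name chronic respiratory disease and lung lesions, not smoking, and the design and COPD adjustment respond to those.
- *Symptoms are certain to be falsely credited.* No figure in the protocol establishes this. With weak smoking effects the bias is negligible.

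All the illustrated odds ratios also lie below the value of 2 that the sample-size paragraph treats as diagnostically useful. Symptoms are selected by p-value, however, and not by the size of the odds ratio, so a moderate bias can still affect entry.

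**Conclusion.** The point holds in a limited form. The stated adjustment set has one smoking main effect, undefined in its levels and unable under any coding to grade ex-smokers by exposure. Neither the interaction clause nor the stepwise rule guarantees a pack-years main effect. Adjusted symptom odds ratios may therefore carry residual confounding by cumulative smoking.

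The direction is upward if smoking raises both cancer risk and the symptom. The amount is unknown and rests wholly on the assumed smoking distribution and slopes: negligible at the weak end, and enough at the strong end to raise the chance of selecting a null symptom well above 5%, even with three-level status and COPD in the model. Age was not simulated and could reduce it further. The matter is confined to the interpretation of IPCARD-SPN and does not touch the primary accuracy or economic outcomes. It is worth correcting because the correction is nearly free.

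**What to change.** In both adjustment statements in Appendix 6, Data Analysis, replace the current smoking term by smoking status (never, former, current) and pack-years (continuous, 0 for never-smokers). State that both are forced into every adjusted symptom model, including each step of the stepwise selection, and keep the planned pack-years interactions in addition.

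The cost is a few words and one or two extra parameters, from data already collected. The drawback is that recall of amount smoked will sometimes be missing or imprecise, and answers given in cigars or loose tobacco need a stated conversion to pack-years.
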